### Economic evaluation

An economic evaluation will be conducted from a societal perspective. All relevant costs will be assessed, valued and analysed. Costs will include costs of the interventions (Go4it programme and usual care), but also other health care related costs. For example, costs of visits to general practitioners, psychologists, physiotherapists, dieticians, paediatricians will also be estimated as well as costs of medication. Indirect costs of production loss are not relevant in this population of teenagers. Relevant cost data will be collected through cost diaries [37]. Costs will be valued according to guidelines for economic evaluation in the Netherlands. Primary outcomes in the economic evaluation will be quality of life, BMI, physical activity and dietary behaviour. The economic evaluation will be performed according to the intention-to-treat principle. A cost-effectiveness analysis will be performed. The mean differences in total costs between intervention groups will be estimated and bootstrapping will be used to estimate 95% confidence intervals.

Cost-effectiveness ratios will be estimated using bootstrapping techniques and graphically presented on cost-effectiveness planes. The incremental cost-effectiveness ratio expresses the additional costs of the Go4it programme per unit improvement of effect. Acceptability curves will also be presented in which the probability that the programme is cost-effective is expressed as a function of willingness-to-pay.

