### Intervention

Go4it is a multidisciplinary group treatment for obese children that is based on the programmes of Braet et al [11], Epstein et al [13] and the materials of the Dutch Obesity Intervention in Teenagers (DOiT) [11,14]. During 7 sessions with an interval of 2–3 weeks the adolescents received education on dietary behaviour, physical activity and energy balance. They also received cognitive behavioural therapy in which they were learned how to improve their lifestyle regarding a healthy weight and how to maintain an adequate energy balance. Go4it was carried out multidisciplinary in an outpatient clinic with a dietician, paediatrician/endocrinologist and psychologist involved. The first session was focussed on increasing awareness of the current lifestyle. Besides dietary and activity journals, step counters (pedometers) were used to increase awareness of the actual behaviour. Next, the adolescents had to set goals with respect to improving their energy balance behaviour. Additionally cognitive-behavioural therapy characteristics were used, e.g. learning to cope with difficult situations (parties, holidays) and teasing. Go4it works with homework tasks and the education is interactive. After 6, 14, 26, and 36 weeks, booster group sessions were scheduled in order to encourage the adolescents to maintain or further improve their energy balance behaviour and to discuss possible problems or questions. In addition, two separate sessions for the parents were organised. These parental sessions consisted of education concerning the health risks of overweight, healthy physical activity and dietary behaviour and how to support their children. Special materials were developed for this program; an information book, a workbook, and a dietary and activity diary. In addition, specific worksheets for every session were developed. The control group received the current regular care, consisting of referral to a dietician in the home care setting.

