#### - Physical activity and sedentary behaviour

The Activity Questionnaire for Adolescents & Adults (AQUAA), is based on the Short Questionnaire to Assess Health-enhancing physical activity (SQUASH)[30]. This questionnaire was not designed to asses' energy expenditure, but to give an indication of the habitual activity level and sedentary behaviour. The AQuAA questionnaire is structured in commuting activities, leisure time activities, household activities, and activities at work and school. For every item examples of activities are provided. The test-retest reliability and validity are currently being studied (Chin A Paw et al, submitted).

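### The societal economic evaluation dismisses production loss because participants are teenagers, a reason that does not cover the parents, for whom Go4it schedules two sessions

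*Protocol article*

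**What the plan says.** The Economic evaluation section of the protocol article sets a broad scope: "An economic evaluation will be conducted from a societal perspective. All relevant costs will be assessed, valued and analysed". The abstract also calls the evaluation societal.

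The same section then names what will be counted: "Costs will include costs of the interventions (Go4it programme and usual care), but also other health care related costs". The examples are all health care: "costs of visits to general practitioners, psychologists, physiotherapists, dieticians, paediatricians will also be estimated as well as costs of medication". The only cost outside health care that it mentions is lost production, and it sets this aside: "Indirect costs of production loss are not relevant in this population of teenagers". Cost data are to come from cost diaries, whose items are not listed, and are to be valued by Dutch guidelines for economic evaluation.

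The Intervention section makes parents part of the programme. After the 7 core sessions and 4 boosters for the adolescents, it says: "In addition, two separate sessions for the parents were organised". The control arm is sent to a home-care dietician, and no parent session is described there.

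**The concern.** A societal perspective counts costs whoever bears them, including family members. The reason given for leaving out production loss looks only at the adolescents. Parents are of working age as a rule, and the programme asks for their time in one arm by design. A cost that arises mainly in one arm does not cancel in the difference between arms.

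The planned outputs are the difference in mean total costs, the incremental cost-effectiveness ratio, the cost-effectiveness plane and the acceptability curve. All take the incremental cost as input. If parent costs are higher under Go4it and are left out, all of them shift towards Go4it, and a reader told that the result is societal would assume that family costs were in it. Cost-effectiveness is one of the two aims stated in the Background, so the label and the content should agree.

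**Working it through.** The article gives no cost figure, session length or wage, so there is nothing to reproduce. The check is a comparison of sections followed by an illustration.

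**Comparison**

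| Item | Go4it arm | Control arm | Named in the cost plan? |
|---|---|---|---|
| Programme or usual care | yes | yes | yes |
| Other care visits, medication | possible | possible | yes |
| Parent sessions: parents' time and work loss | 2 sessions scheduled | none described | no; production loss dismissed by reference to teenagers |
| Family travel | outpatient clinic | home-care dietician, number of visits not given | not named, not excluded |

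**Direction**

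Let *d* be the mean parent cost per family under Go4it minus that under usual care. The reported incremental cost is then the societal one minus *d*. It is too low, in favour of Go4it, whenever *d* > 0. The two parent sessions make *d* > 0 the likely case. They do not prove it, because parent time in the control arm is unknown.

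**Illustration**

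From the article: 2 parent sessions. Assumed: one parent per family attends, 2–3 hours per session including travel time, 10–25 euro per hour.

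- Parent hours per Go4it family: 2 × 2 = 4 to 2 × 3 = 6.
- Gross value: 4 × 10 = 40 euro to 6 × 25 = 150 euro.
- With wider assumptions of up to 4 hours and 30 euro per hour, the upper end is 2 × 4 × 30 = 240 euro.

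These are gross amounts for one arm. The net amount is (4 to 6 hours minus control-arm parent hours) × hourly value. On these assumptions it would vanish if control parents spent 4–6 hours on care visits beyond any comparable time spent by Go4it parents. The article does not allow that figure to be filled in.

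**The case against.** Several arguments on the other side have force.

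- **The cost list is open.** The section promises that "All relevant costs will be assessed, valued and analysed", and it introduces its items as inclusions and examples. Travel and out-of-pocket costs are not excluded, and the diary may record them. A design article commonly leaves diary items to fuller documents. This stands: a reader might infer that the evaluation counts health-care costs only and is simply a health-care evaluation under another name, but the text does not establish that.
- **The exclusion may concern participants only.** The sentence can be read as saying that the adolescents' own wage loss is negligible, with parents not considered. This is a fair reading, but it does not remove the problem. The sentence is the only statement on productivity, and anyone following it would cost none.
- **Parents accompanying the adolescents is not documented.** One could add the 7 core and 4 booster sessions to reach 13 visits and 13 × 3 × 25 = 975 euro. Nothing says that parents attend those 11 sessions, so that figure should not be used.
- **Paid work by participants is not documented.** The activity questionnaire covers "leisure time activities, household activities, and activities at work and school", but it is a generic instrument for adolescents and adults. Its work domain is no evidence that these participants hold jobs.
- **Controls also have care visits.** Their number is not given, and parents may spend time on them. The direction of bias is therefore an inference, and its size is unknown.

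What remains is narrower but firm: a stated reason that does not cover parents, beside an intervention that schedules their time.

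**Conclusion.** The point holds in limited form. A societal perspective is declared, productivity is dismissed on a ground that fits only the adolescents, and parents have scheduled sessions in the Go4it arm with no described counterpart. This is a stated rule with an incomplete reason, not a detail left for a fuller document.

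If the rule is applied as written, the incremental cost of Go4it is probably understated. Only the two parent sessions rest on the article; 40–150 euro per Go4it family is an illustration on assumed hours and values, before any control-arm offset. Whether such an amount matters cannot be judged, because the programme's own cost is not given.

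A reader might go further and conclude that the trial cannot answer its economic question. That does not follow from one cost component that may be missing. The primary outcome, BMIsds, is untouched. The point is worth correcting because the correction is cheap and the result will be read as societal.

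**What to change.** Limit the production-loss sentence to the participants. State that parents' lost work or time, and family travel, are recorded in the cost diaries of both arms and valued by the Dutch guidelines that the plan already invokes. Collecting them in both arms matters, because only the difference enters the incremental cost.

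If the diaries are already fixed and lack these items, add a scenario analysis that imputes parent time from attendance at the parent sessions, with the assumed hours and hourly value stated and varied. Describe the main analysis as excluding parental productivity and time costs. Call it a health-care perspective only if the diaries record no family costs at all.

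The cost is a few diary items or a small calculation from attendance records, plus wording. The incremental cost of Go4it may become less favourable. Randomisation, clinical outcomes and sample size are not affected.

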## Discussion

The Go4it program will be evaluated in a randomised controlled trial including an economic evaluation. We will determine the effectiveness and cost-effectiveness of this program, regarding body composition, energy requirement, dietary and physical activity behaviour, quality of life and body self esteem. The results of this study contribute to the evidence based knowledge of how to improve dietary, physical activity and sedentary behaviour among obese adolescents and how these behaviours affect weight and the development of Diabetes Mellitus type 2.
